**Figure 2 figure2:**
[figure not shown]
Screenshots of the Ned app. (a) Graphical view of prostate-specific antigen (PSA) results; (b) Ned’s Notes; and (c) the Expanded Prostate Cancer Index Composite (EPIC-26) survey.

### Data Collection

#### Adoption of Ned

Our decision to study the adoption of Ned by patients, caregivers, and clinicians was informed by previous pivotal evaluative work on the adoption, nonadoption, and abandonment of a personal electronic health record in the United Kingdom. Greenhalgh et al’s [41] focus on adoption as a primary study outcome revealed a complex and dynamic narrative between patients and health care “experts:” there is a discrepancy between the expectations placed on patients to adopt health technology perceived as beneficial to them, and the reality of what patients actually perceive as beneficial for their own health and well-being [41]. We have therefore selected adoption as a core outcome for our own study and seek to identify the realist context-mechanism-outcome configurations to explain how Ned is adopted (or not) by its users. We define adoption as the active translation of intention into measurable action; this is operationalized as the number of patients, caregivers, and clinicians who are invited to open a Ned account and the consequent number of Ned accounts created.

#### Acceptability of Ned

To achieve effective health promotion using health technology, it is essential that patients perceive a given treatment to be an acceptable and welcome addition to their care [42]. The acceptance of technology has been widely studied, with efforts made in recent years to contextualize this understanding within the health care domain [43]. We define acceptability here as the behavioral intention to use a technology, leading to actual use and consequent use behaviors. For this work, we have chosen to frame our measurement of acceptability through adapting and operationalizing the unified theory of acceptance and use of technology (UTAUT) model [42] into a quantitative questionnaire (Multimedia Appendix 1). The UTAUT is a theoretical model and instrument used to assess the likelihood of user acceptance for a new technology. It has been extensively used to evaluate the factors affecting the acceptance and use of new health technologies [44], including in an evaluation of patient acceptance of an automated text messaging system for improved prostate cancer screening adherence [45]. While the original model identifies 7 predictor constructs for behavioral intention (ie, performance expectancy, effort expectancy, social influence, facilitating conditions, hedonic motivation, price value, and habit), we felt it appropriate to modify the model to better align with the context in which Ned will be implemented. We have therefore removed 2 constructs from the overall model, hedonic motivation and price value, and have also added baseline belief in treatment credibility and outcome expectancy as a predictor variable for both behavioral intention and use behavior.

Our justifications for these decisions are as follows: hedonic motivation, defined as enjoyment while using technology, is not a relevant construct to evaluate Ned given that the app was designed to deliver PSA results, which are a source of anxiety for many prostate cancer survivors [9]. Previous research on patient portal acceptance using the UTAUT model has also recommended the removal of this construct, with the rationale that health technology primarily designed to deliver condition-specific information is intrinsically driven by the presence of a health *problem* —something that does not promote enjoyment [46]. Price value was also not an applicable construct for Ned, since patients will be receiving the app for free and will therefore be unable to comment on its value for money. Finally, we are asking patients to rate their belief in the treatment credibility and outcome expectancy of Ned to improve their survivorship care [47]. The degree to which patients initially believe that a given treatment will benefit their health and well-being has been shown to strongly affect treatment outcomes for chronic conditions [48]. We posit that a patient’s initial belief in Ned will correlate with their ultimate acceptance of the app for survivorship care.

#### Effectiveness of Ned

While a substantial amount of research has been done to address the functional impairments caused by prostate cancer treatments, less emphasis has been placed on alleviating the psychological and emotional barriers faced by survivors throughout their survivorship experience. There is recognition that, while overall satisfaction with prostate cancer follow-up care is high, the presence of problematic treatment-related side effects is associated with higher psychological morbidity, poorer self-efficacy, greater unmet needs, and poorer overall health status [49]. Strategies for identifying those men with ongoing problems, alongside new interventions and models of care tailored to individual needs, are needed to improve quality of life. Novel solutions have been devised, notably the successful implementation of a real-time dashboard platform to integrate prostate cancer-specific PROMs into clinical settings that resulted in higher patient quality of life and satisfaction with care [10]. We are encouraged by this work and seek to explore whether our own technology, which combines the collection of PROMs with the provision of PSA values, can achieve similar outcomes. To establish the degree to which Ned can significantly improve how prostate cancer survivors experience their care, we chose to investigate the app’s impact on 5 specific clinical outcomes: health-related quality of life, satisfaction with cancer care, unmet needs, self-efficacy, and prostate cancer-related level of anxiety. We have operationalized our outcomes using a collection of existing validated questionnaires that have been widely used in prostate cancer survivorship research to standardize our work and facilitate future meta-analyses [50]. We have also selected a data collection schedule matching that of the largest prostate cancer survivorship study ever conducted to enable the comparison of any generated data trends with existing population baseline data [8]. In addition to collecting outcomes data, we will also review patient charts to collect the following clinical variables: Gleason score, cancer stage, treatment group (ie, active surveillance, postsurgery, castration resistant, postradiation, postsalvage radiation, and hormone sensitive), and comorbidities. Table 2 lists the data collection schedule for all outcome measures.

**Table 2 table2:** Data collection schedule for outcomes measures.

Measure	Data collection method	n	Baseline	2 months	6 months	12 months
Use data	Log data analytics software	610	Throughout study duration			
Demographic data	Web-based questionnaire	400	x			
Clinical data	Chart review	400	x			
Credibility/Expectancy questionnaire	Web-based questionnaire	400	x			
Expanded Prostate Cancer Composite	Web-based questionnaire	400	x	x	x	x
Prostate Cancer-Related Quality of Life Scales	Web-based questionnaire	400	x			
Service Satisfaction Scale for Cancer Care	Web-based questionnaire	400	x	x	x	x
Supportive Care Needs Survey	Web-based questionnaire	400	x	x	x	x
Self-Efficacy for Managing Chronic Disease Scale	Web-based questionnaire	400	x	x	x	x
Memorial Anxiety Scale for Prostate Cancer	Web-based questionnaire	400	x	x	x	x
Modified UTAUT^a^ survey	Web-based questionnaire	400				x
Patient qualitative interviews	(1) Semistructured live interview (2) Qualitative observation of app use	20				x
Caregiver qualitative interviews	Semistructured live interview	10				x
Clinician System and Use Assessment Survey	Web-based questionnaire	10				x

^a^UTAUT: unified theory of acceptance and use of technology.

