#### Ned: A Prostate Cancer Survivorship App

The recent endorsement of mHealth, broadly defined as a health intervention that has been operationalized into an app for patient use and is delivered or supported through the use of wireless devices (eg, mobile phones, tablets, media players, wearables), has been lauded as a promising complement to current outpatient treatment and monitoring strategies for chronic care [23]. In particular, the ubiquity of mobile phone use has facilitated the adoption of mHealth apps for immunization record keeping [24], heart health [25], and diabetes self-management [26]. In November 2012, a proof-of-concept mHealth app prototype for personalized prostate cancer survivorship care was conceptualized at the Hacking Health Codeathon in Toronto, Canada [27]. From 2014 to 2017, the app was translated from prototype to product, and a user-centered needs assessment and usability evaluation were conducted to inform app content and functionality (University Health Network Research Ethics Board [REB] ID#14-7510). Ned (No Evident Disease) is the first app to provide patients with access to individual-level PSA values streamed directly from the Ontario Laboratories Information System (OLIS) to their own smartphone. The mHealth app for patients and their caregivers, along with a clinician-facing app and complementary Web-based dashboard, were developed using Fast Healthcare Interoperability Resources, which facilitate interoperability with existing Canadian provincial and federal health care assets [28]. Ned aims to promote self-care by informing patients directly of their PSA results and providing them with a personalized view of their own symptoms. It supports real-time clinical decision making by providing clinicians with PROMs collected in-app, and includes a curated educational feed and support group links. Ned is not meant to take the place of an informative discussion between patient and provider; however, there is an acknowledgement that, in reality, patient-provider interactions may be brief, and patients may require additional communication channels, which may lead to more meaningful interactions and improve shared decision making.

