Clinical effectiveness of Ned	Five validated patient-reported outcome measures (ie, quality of life, treatment satisfaction, unmet needs, self-efficacy, anxiety) administered at baseline, 2 months, 6 months, and 12 months

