#### Health-Related Quality of Life

We will assess prostate cancer-specific quality of life and functional recovery after treatment using the EPIC-26 [39]. The EPIC-26 is a reliable and valid scale with 26 items assessing 5 health domains: urinary continence, urinary irritation, sexual function, bowel function, and hormonal expression. It is scored on a summary scale from 0 to 100, with higher scores corresponding to higher health states. We will also use the Prostate Cancer-Related Quality of Life Scales [51] to complement the EPIC-26, as the scales are designed with a stronger focus on patient perception and derived meaning from treatment outcomes. Each individual scale contains between 2 and 8 items and is rated on a 5-point Likert scale. We will specifically be using the following 6 scales: Health Worry, PSA Concern, Cancer Control, Informed Decision, Regret, and Outlook.

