#### Quantitative Survey Data

Descriptive statistics will first be conducted on all variables to identify methodological data trends and parameters. We will analyze differences in baseline demographic and clinical variables using Pearson chi-square and nonparametric Wilcoxon rank sum tests. Given that we will be asking the same patients to complete repeated outcome measures across 4 time periods, we will account for autocorrelation effects through the use of linear generalized estimating equations, which are a multivariate analog of linear regression for longitudinal data and recommended for use in longitudinal repeated-measures data analyses [65,66]. Our data analysis strategy to answer the following questions is as follows:

(1) What is the effect of Ned on health-related outcomes over time? To assess the effect of Ned on quality of life, satisfaction with cancer care, unmet needs, self-efficacy, and prostate cancer-related level of anxiety domains, we will use generalized estimating equation models containing indicators for each study time point to assess whether the average study assessment scores at 2 months, 6 months, and 12 months were significantly different from baseline values.

(2) Is there a relationship between patient engagement with Ned and changes in health-related outcomes over time? We will explore whether patients who engage with the content and functionality of the app experience improvements in their health and well-being by building linear regression models for use and outcomes data.

(3) Is there a relationship between health-related outcomes? To understand whether changes in health-related outcomes share a similar direction and magnitude, we will perform Pearson correlation analyses to test for a correlational relationship between outcome variables.

(4) Do demographic and clinical variables affect changes in health-related outcomes? We will first conduct independent *t* tests and 1-way independent analyses of variance to determine whether there were differences in health-related outcomes for all categorical demographic and clinical variables, and Pearson correlation analyses for all continuous variables. We will then perform multiple linear regression analyses with health-related outcomes as dependent variables and all significant predictor variables from our preliminary analyses as independent variables.

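### The six Prostate Cancer-Related Quality of Life Scales are presented as an effectiveness measure but scheduled at baseline only, so the planned comparison with baseline cannot be made on them

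*Protocol article*

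**What the plan says.** In the protocol article, the section Effectiveness of Ned names health-related quality of life as one of five outcomes on which the app's impact will be investigated. It then introduces the schedule: "Table 2 lists the data collection schedule for all outcome measures".

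The section Health-Related Quality of Life measures that outcome with two instruments. EPIC-26 is described first, and then: "We will also use the Prostate Cancer-Related Quality of Life Scales [51] to complement the EPIC-26". Six scales are selected: "Health Worry, PSA Concern, Cancer Control, Informed Decision, Regret, and Outlook".

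In Table 2 the row "Prostate Cancer-Related Quality of Life Scales" (web-based questionnaire, n=400) carries one mark, under baseline. The cells for 2, 6 and 12 months are empty.

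In Table 1 the clinical-effectiveness unit consists of five validated patient-reported measures, "administered at baseline, 2 months, 6 months, and 12 months".

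Under Quantitative Survey Data, Question 1 estimates the effect of Ned with generalized estimating equations that test whether "average study assessment scores at 2 months, 6 months, and 12 months were significantly different from baseline values".

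**The concern.** An instrument chosen to measure an effectiveness outcome needs at least one value after exposure to the intervention. These scales have none. Patients answer them before they receive a Ned account and never again, so nothing can be said about change on them.

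The gap has some substance. The five EPIC-26 domains (urinary continence, urinary irritation, sexual, bowel, hormonal) are mostly functional. The article motivates its choice of outcomes by saying that functional impairment has been studied more than the psychological and emotional side of survivorship. The additional scales were chosen "to complement the EPIC-26, as the scales are designed with a stronger focus on patient perception and derived meaning from treatment outcomes". As scheduled, change in quality of life rests on EPIC-26 alone, and the instrument added for the patient's perspective contributes nothing to the pre-post comparison.

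**Working it through.** The point turns on the schedule, and the article gives no figure to reproduce. The rows of Table 2 can be set beside the role the text gives each instrument.

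| Instrument (Table 2) | Baseline | 2, 6, 12 months | Role stated in the text |
|---|---|---|---|
| EPIC-26 | yes | yes, all three | quality-of-life outcome |
| Service Satisfaction Scale | yes | yes, all three | satisfaction outcome |
| Supportive Care Needs Survey | yes | yes, all three | unmet-needs outcome |
| Self-efficacy scale | yes | yes, all three | self-efficacy outcome |
| Memorial Anxiety Scale | yes | yes, all three | anxiety outcome |
| Demographic and clinical data | yes | no | explanatory variables in Question 4 |
| Credibility/Expectancy questionnaire | yes | no | predictor in the modified acceptance model |
| Prostate Cancer-Related Quality of Life Scales | yes | no | quality-of-life outcome, complementing EPIC-26 |

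1. *Is the empty row an artefact of text extraction?* It does not look like one. It has the same layout as the other baseline-only rows, and the rows around it are intact.

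2. *Do the other baseline-only rows have a reason?* Yes. Demographic and clinical variables enter Question 4, and the Acceptability section explains why baseline belief is measured as a predictor. The quality-of-life scales are the only baseline-only row presented as an outcome, and the text gives no other role for them.

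3. *What can the Question 1 model estimate?* It has 3 contrasts with baseline per score. With 1 planned assessment and 0 after baseline, the number estimable is 0 of 3 for each scale, or 0 of 6 × 3 = 18 across the six. Questions 2 and 4, which concern changes in outcomes, cannot use the scales as change outcomes either, nor can Question 3 where it concerns changes.

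4. *Does Table 1 contradict Table 2?* No. Table 1 counts five repeated measures, and Table 2 repeats exactly five instruments, with EPIC-26 as the quality-of-life one.

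5. *Which content is covered elsewhere at follow-up?* The Memorial Anxiety Scale has a PSA-related anxiety subscale as well as subscales for prostate cancer anxiety and fear of recurrence. The needs survey has psychological and health system and information domains. The satisfaction scale covers health information. All three are repeated. Informed Decision, Regret, Cancer Control and Outlook are not named as domains of any repeated instrument.

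6. *What would follow-up cost in items?* The article gives 2 to 8 items per scale, so 6 × 2 = 12 to 6 × 8 = 48 items per administration. The repeated questionnaires have about 26 + 16 + 34 + 6 + 18 = 100 items (taking the modified needs survey to keep 34). One added administration is 12 to 48 items; three would be 36 to 144.

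**The case against.** The strongest reply is that baseline-only collection may be deliberate. EPIC-26 is the powered measure, the scales only complement it, and Table 1's count of five leaves them out. A single baseline score could describe the cohort or help explain for whom the app works, which suits a realist evaluation, and a journal article may leave that rationale to a fuller protocol. This stands as a possibility. It does not remove the problem, because the article presents the scales as a measure of an effectiveness outcome and, unlike the Credibility/Expectancy questionnaire, gives them no predictor or descriptor role.

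Burden is also a fair objection. Patients already face about 100 items per assessment plus monthly in-app questionnaires, and 20% dropout is expected. That weighs against repeating the scales at every visit, but much less against adding them once.

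A reader might go further in three ways that the article does not support:

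- *That Tables 1 and 2 contradict each other.* Both give five repeated measures.
- *That these are the scales closest to what Ned does.* The article says "Ned aims to promote self-care by informing patients directly of their PSA results", and PSA Concern and Informed Decision sound related. That is a judgement from scale names, no item content is shown, and neighbouring constructs are measured at all four assessments.
- *That more than half of the quality-of-life scores are lost.* Counting six scales against five EPIC-26 domains gives 6 of 11, but the article defines no such total, and the ratio gives a supplementary instrument more weight than the powered one.

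**Conclusion.** The point holds in a limited form. Six scales presented as part of the quality-of-life outcome have no follow-up assessment, so none of their 18 possible contrasts with baseline can be estimated. Up to 400 patients would answer 12 to 48 items that cannot enter the pre-post analysis.

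The damage stops there. The EPIC-26 comparison, its sample size and the other four repeated outcomes are untouched, so it would be wrong to conclude that the study cannot estimate change in quality of life or in PSA-related anxiety. What is lost is change on these particular scales, most clearly on the four whose content no repeated instrument is said to cover. This rests on Table 2 as printed being the schedule in force. The remedy is an inexpensive improvement to the schedule, or failing that a clarification.

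**What to change.** In Table 2, mark the Prostate Cancer-Related Quality of Life Scales at 12 months. Analyse the 12-month versus baseline change as a secondary quality-of-life outcome in the Question 1 model, with that single follow-up contrast for each scale.

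The cost is a schedule change and 12 to 48 extra items in a web assessment patients already complete; that assessment also carries the acceptance survey. On the article's timeline (first recruit October 2017), 12-month assessments begin about October 2018, so baseline answers already given could be paired if the change is made before then. Adding the scales at 2 and 6 months too is a debatable trade against burden and is not needed to close the gap.

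If baseline-only collection is intended, say so: state that the scales are baseline descriptors or predictors, name the analysis that uses them, and stop presenting them under the effectiveness outcome. That costs only a change of text.

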#### Health-Related Quality of Life

We will assess prostate cancer-specific quality of life and functional recovery after treatment using the EPIC-26 [39]. The EPIC-26 is a reliable and valid scale with 26 items assessing 5 health domains: urinary continence, urinary irritation, sexual function, bowel function, and hormonal expression. It is scored on a summary scale from 0 to 100, with higher scores corresponding to higher health states. We will also use the Prostate Cancer-Related Quality of Life Scales [51] to complement the EPIC-26, as the scales are designed with a stronger focus on patient perception and derived meaning from treatment outcomes. Each individual scale contains between 2 and 8 items and is rated on a 5-point Likert scale. We will specifically be using the following 6 scales: Health Worry, PSA Concern, Cancer Control, Informed Decision, Regret, and Outlook.

#### Satisfaction with Cancer Care

We will assess patients’ satisfaction with their treatment outcomes using a cancer care-specific adaptation of the Service Satisfaction Scale [52,53]. This scale is often used in combination with the EPIC-26 to capture the relationship between quality of life and satisfaction with outcomes [8]. It consists of 16 items and measures several aspects of satisfaction, including satisfaction with outcomes, provider manner and skill, health information, and access. Responses are scored and converted to a scale from 0 to 100, with higher scores indicating higher levels of patient satisfaction.

#### Unmet Needs

We will use the 34-item Supportive Care Needs Survey Short Form (SCNS-SF34) [54] to assess a patient’s current level of need across 5 domains: psychological, health system and information, physical and daily activity, patient care, and support and sexuality. This validated instrument has been previously used in prostate cancer survivorship studies, where it led to the determination that the most prevalent unmet needs are related to sexual issues, concerns about significant others, and anxieties around the possibility of recurrence [9]. We will be using a modified version of the SCNS-SF34 with a simplified response format, which was validated for use with prostate cancer survivors [55].

